## 3.2 Analysis of the CDMP cohort

### 3.2.1 Utilisation patterns over-time

For outcomes defined as number of events (hospital and ED admissions), we will calculate rates and their 95% CI for every 6-month period between January 2011 and December 2013. Death will be considered as a censoring event i.e. if a participant dies after four months in a given semester, the event rate will only be calculated over 4 months.

Results will be presented on a plot, first for all program participants together and then separately depending on the enrolment semester to identify potentially different patterns between those enrolled early vs late into the program.

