## 1 Data sources

### 1.1 The Chronic Disease Management Program Minimum Data Set

The analysis will include every participant recorded in the program minimum dataset and enrolled between January 2011 and December 2013. The date of enrolment will be calculated using the following approach: If the Program consent date is available, it will be used as the enrolment date. If it is missing, and the Enrolment decision date is available, then this date will be used. If this is also not available, then the Registration date will be used as enrolment date instead.

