### 1.2 APDC

The APDC dataset will contain every public and private hospital admission which occurring between January 2007 and December 2013 in NSW. CDMP participants will be flagged.

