### 1.3 EDDC

The APDC dataset will contain every public and private emergency department admission occurring between January 2007 and December 2013 in NSW. CDMP participants will be flagged.

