### 3.2.2 *Before-after analyses*

Before-after analyses using will compare the rate of hospitalisations before enrolment into the program to the rate after enrolment into the program. For the before-after comparison, only patients enrolled between January 11 and June 13 will be included while only counting events occurring between 1 July 2010 (6 months before January 11) and 31 December 2013 (6 months after June 13).

For the purpose of this analysis every program participant will therefore contribute 2 data points; one before enrolment and one after enrolment. The analysis will be a Poisson regression with the period (before vs after) as a fixed effect. Generalized estimating equations with a compound symmetry structure will be used to model the correlations between multiple measurements from each patient.

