### 3.2.3 *Time-dependent analyses*

Time-dependent analyses will be used to assess the impact of “exposure to the program” on the rate of hospitalisations. Exposure to the program will be defined for each semester as the proportion of the time a participant was exposed to the program e.g. if a patient gets enrolled into the program halfway through a semester, his/her exposure will be 50% (s/he was on the program 50% of the time during that particular semester).

The time-dependent analysis will cover a total of 6 semesters. All patients enrolled between January 2011 and December 2013 will be included and all events occurring within the same timeframe will be considered. For the purpose of this analysis every program participant will therefore contribute 6 data points; one per semester. The analysis will be a Poisson regression with the exposure proportion as a fixed effect. A sensitivity analysis will also include the semester and its interaction with exposure. Generalized estimating equations with a compound symmetry structure will be used to model the correlations between multiple measurements from each patient

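### The early-versus-late utilisation plots in SAP section 3.2.1 cover the same 36 months as enrolment, so enrolment cohort is confounded with stage relative to enrolment: fully for the first versus last cohort (apart from the mixed enrolment semester) and partly for the others

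*SAP*

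**What the plan says.** Section 3.2.1 (Utilisation patterns over-time) sets the window: "we will calculate rates and their 95% CI for every 6-month period between January 2011 and December 2013". The rates are plotted for all participants together and then "separately depending on the enrolment semester to identify potentially different patterns between those enrolled early vs late into the program". The time axis is calendar time, and no alignment on enrolment date is specified. Death censors a participant's time at risk.

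Section 1.1 defines the analysed cohort as participants "enrolled between January 2011 and December 2013", which is the same window.

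The event data reach further back. Section 1.2 obtains "every public and private hospital admission which occurring between January 2007 and December 2013 in NSW", and section 1.3 obtains "every public and private emergency department admission occurring between January 2007 and December 2013 in NSW".

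The next analysis, section 3.2.2, allows for both sides of enrolment. It restricts enrolment to January 2011 through June 2013 while "only counting events occurring between 1 July 2010 (6 months before January 11) and 31 December 2013 (6 months after June 13".

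**The concern.** The split plots have one stated purpose: to show whether early and late enrollees use services differently. When the plotting window equals the enrolment window on a calendar axis, early cohorts contribute mostly post-enrolment time and late cohorts mostly pre-enrolment time. A gap between their curves may reflect who enrolled when, or only where each cohort stands relative to enrolment. The display does not separate the two.

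A second loss follows. Section 3.2.2 compares one rate before with one rate after enrolment and has no time trend. The main model of section 3.2.3 has exposure proportion as its fixed effect, with semester entering only in a sensitivity analysis. The section 3.2.1 plots are therefore the natural place to see whether use was already rising or peaking before enrolment. For the January-June 2011 cohort, which has the longest follow-up, they show no full pre-enrolment semester.

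**Working it through.** **Inputs.** Plot window January 2011 to December 2013 (section 3.2.1). Enrolment window the same (section 1.1). Hospital and ED data from January 2007 to December 2013 (sections 1.2 and 1.3). Before-after window from 1 July 2010, with enrolment cut at June 2013 (section 3.2.2).

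**The plan's own figure.** 36 months / 6 = 6 semesters, which agrees with the six semesters stated in section 3.2.3 for the same window.

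**Count by cohort.** Number the enrolment semesters k = 0 (January-June 2011) to k = 5 (July-December 2013). Cohort k has k full semesters before enrolment, one mixed semester containing enrolment, and 5 - k full semesters after. If enrolment is uniform within the semester (an assumption; the SAP gives no distribution) and deaths are ignored, mean pre-enrolment time is 6k + 3 months and mean post-enrolment time is 36 - (6k + 3) months.

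| Cohort | k | Full semesters pre / mixed / post | Mean months pre / post |
|---|---|---|---|
| Jan-Jun 2011 | 0 | 0 / 1 / 5 | 3 / 33 |
| Jul-Dec 2011 | 1 | 1 / 1 / 4 | 9 / 27 |
| Jan-Jun 2012 | 2 | 2 / 1 / 3 | 15 / 21 |
| Jul-Dec 2012 | 3 | 3 / 1 / 2 | 21 / 15 |
| Jan-Jun 2013 | 4 | 4 / 1 / 1 | 27 / 9 |
| Jul-Dec 2013 | 5 | 5 / 1 / 0 | 33 / 3 |

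The minority period in each extreme cohort averages 3/36, about 8% of its plotted time. For an individual it ranges from 0 to 6 months.

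**Stage at one calendar point.** In calendar semester s (0 to 5), cohort k is at relative semester s - k. In January-June 2013 (s = 4) the first cohort is at +4 and the last at -1. Two different cohorts never have the same s - k at the same s. One common course around enrolment would therefore still produce separated curves, unless that course were flat.

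**Overlap in relative time.** Cohort k covers relative semesters -k to 5 - k, so cohorts d apart share 6 - d of them. Of the 15 pairs, 5, 4, 3, 2 and 1 pairs share 5, 4, 3, 2 and 1 relative semesters. Only first versus last shares the enrolment semester alone. Cohorts k = 1 and k = 4 share -1, 0 and +1. A shared full semester on both sides needs both cohorts within k = 1 to 4, which is 4 × 3 / 2 = 6 of the 15 pairs.

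**After an earlier start.** From July 2010 (7 semesters) cohort k has k + 1 full pre-enrolment semesters, that is 1 to 6. From January 2007 (14 semesters) it has k + 8, that is 8 to 13. The post-enrolment count stays at 5 - k. With either start, cohorts k = 0 to 4 all have full semesters on both sides, so 5 × 4 / 2 = 10 of the 15 pairs share them. The five pairs that include the last cohort still do not.

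**The case against.** The best defence is that the figure is descriptive. It carries no test and no effect estimate, and the program effect rests on the matched cohort in section 3.3.1. The curves are drawn by enrolment semester, so a careful reader can locate each cohort's enrolment on the axis. Section 2.2 tabulates 2010 hospital and ED use by year of enrolment, which gives all cohorts a common pre-program year. The window also matches the six-semester analysis in section 3.2.3. All of this stands and keeps the point small. It does not remove it: the 2010 figures are annual totals without a trend, and section 3.2.1 does not ask for curves to be read at matched stages.

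A reader might infer more than the document supports:

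- That the early-versus-late comparison is impossible. It is not: the four middle cohorts have full semesters on both sides, and only one pair of 15 overlaps in the enrolment semester alone.
- That the extreme cohorts show exclusively one side of enrolment. Each has a mixed semester.
- That any difference between curves must be program stage. It could be stage, cohort or both.
- That the older data cure both ends. They supply a baseline for early enrollees, but no follow-up for the last cohort.
- That the 2007-2010 death records are a neglected resource here. People enrolled from 2011 onwards were alive throughout those years.

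**Conclusion.** The point holds as a limitation of a descriptive display. The calendar window coincides with the enrolment window, so the January-June 2011 cohort has no full pre-enrolment semester and the July-December 2013 cohort has no full post-enrolment semester. The early-versus-late contrast is confounded with program stage, completely for that pair apart from the mixed semester and partly for the others. The semester counts follow from the stated dates alone. Only the mean months rest on uniform enrolment within the semester and on ignoring deaths. No estimate of program effect changes, so this is an inexpensive improvement that lets the figure serve its stated aim.

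**What to change.** In section 3.2.1:

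1. Start the hospital and ED series earlier, at least at July 2010 to match section 3.2.2, or at January 2007 where the data begin.
2. Keep the calendar plots and add a version aligned on each participant's enrolment date, by enrolment semester. Both are useful, because cohorts aligned on enrolment sit in different calendar periods.
3. Compare cohorts only at relative semesters that both contribute.
4. State that the July-December 2013 cohort has no full post-enrolment semester because data end in December 2013, and that the earlier start does not change this.
5. Add a caveat that pre-enrolment semesters are conditional on survival to enrolment, while post-enrolment semesters are censored at death.

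The cost is some SAP wording and a few extra plots. No new data are needed, and the primary matched analysis is unaffected.

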### 3.2.2 *Before-after analyses*

Before-after analyses using will compare the rate of hospitalisations before enrolment into the program to the rate after enrolment into the program. For the before-after comparison, only patients enrolled between January 11 and June 13 will be included while only counting events occurring between 1 July 2010 (6 months before January 11) and 31 December 2013 (6 months after June 13).

For the purpose of this analysis every program participant will therefore contribute 2 data points; one before enrolment and one after enrolment. The analysis will be a Poisson regression with the period (before vs after) as a fixed effect. Generalized estimating equations with a compound symmetry structure will be used to model the correlations between multiple measurements from each patient.

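### In the supportive before-after analysis, late enrollees weigh more in the before rate and early enrollees in the after rate, so enrolment time should be in the model

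*SAP*

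**What the plan says.** SAP section 3.2.2 restricts the sample and the counting window by calendar date: "only patients enrolled between January 11 and June 13 will be included while only counting events occurring between 1 July 2010". The window closes at the end of December 2013, so the stated margin is 6 months at each end. The section sets no individual window of equal or fixed length.

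Each person is reduced to two records: "every program participant will therefore contribute 2 data points; one before enrolment and one after enrolment". The model is a "Poisson regression with the period (before vs after) as a fixed effect", and the within-person correlation is handled by GEE with compound symmetry. The outcome is called a rate, but no offset is written out.

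Section 3.2.4 adds a version adjusted for LHD, demographics, ARIA, SEIFA, target conditions, SF1 and 2010 service use. Enrolment date, semester and year are not on that list.

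Section 3.2.1 plots utilisation by enrolment semester, looking for "potentially different patterns between those enrolled early vs late into the program".

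**The concern.** The before and after windows move in opposite directions as enrolment date advances. A person-time offset makes each record a rate, but it also weights each record by its length. The before rate is then mainly that of late enrollees and the after rate mainly that of early enrollees. If the two groups differ in underlying rate, the period coefficient picks up part of that between-person difference.

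A program with no effect could look harmful if higher-rate people enrolled first, or beneficial if they enrolled later. This is separate from regression to the mean: it arises even when every person's own rate is constant.

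**Working it through.** **Inputs from the SAP.** Enrolment runs from January 2011 to June 2013 (30 months), and events count from 1 July 2010 to 31 December 2013 (42 months), both from section 3.2.2. The model there has period as its only fixed effect, with exchangeable GEE. Enrolment time is absent from the list in section 3.2.4.

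**Assumptions, not in the SAP.** Enrolment is uniform, the offset is log person-time, each person's rate is constant, there is no program effect and there are no deaths. The early/late rate ratio *r* runs from 0.5 to 2.0.

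**Step 1: the SAP's own margins.** For enrolment *t* months after 1 January 2011, before = 6 + *t* and after = 36 − *t*. Enrolment on 1 January 2011 gives 6 and 36 months, 1 April 2012 gives 21 and 21, and 30 June 2013 gives about 36 and 6. The stated 6-month margins at each end are reproduced.

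**Step 2: who supplies the time.** The semester midpoints are *t* = 3, 9, 15, 21 and 27.

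| Enrolment semester | Before (months) | After (months) | Share of before | Share of after |
|---|---|---|---|---|
| 1 | 9 | 33 | 9/105 = 8.6% | 33/105 = 31.4% |
| 2 | 15 | 27 | 14.3% | 25.7% |
| 3 | 21 | 21 | 20.0% | 20.0% |
| 4 | 27 | 15 | 25.7% | 14.3% |
| 5 | 33 | 9 | 31.4% | 8.6% |

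**Step 3: null rate ratio without within-person correlation.** With λ the underlying rate, *a* the after time and *b* the before time,

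RR = [Σλa / Σa] ÷ [Σλb / Σb].

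Take a log-linear gradient, λ = r^(1 − t/30). For *r* = 2 the five midpoint rates are 1.866, 1.625, 1.414, 1.231 and 1.072.

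- After: (33×1.866 + 27×1.625 + 21×1.414 + 15×1.231 + 9×1.072)/105 = 1.555
- Before: (9×1.866 + 15×1.625 + 21×1.414 + 27×1.231 + 33×1.072)/105 = 1.328
- RR = 1.555/1.328 = 1.17

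The same formula over continuous *t* gives 1.18 at *r* = 2, 1.10 at 1.5, 1.04 at 1.2, 1.00 at 1, 0.91 at 0.67 and 0.85 at 0.5. If the whole difference were instead a step between the first and second half of enrollees, it would give 1.27 at *r* = 2 and 0.79 at 0.5.

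**Step 4: the plan's GEE, simulated** (log-linear gradient, exchangeable correlation, offset, n = 20,000, an assumed size).

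| Setting | r = 0.5 | r = 1.5 | r = 2 |
|---|---|---|---|
| About 1 event/year, gamma frailty | 0.90 | 1.08 | 1.12 |
| About 1 event/year, no frailty | 0.85 | 1.11 | 1.16 |
| 0.3 events/year, little frailty | 0.87 | 1.11 | 1.18 |

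Stronger within-person correlation shrinks the bias but does not remove it. With equal early and late rates, the IRR was 1.00 to 1.01.

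**Step 5: section 3.2.4 adjustment.** Only 2010 hospital use was modelled. At 0.3 events/year, adding it moved 1.11 to 1.10, 1.18 to 1.15 and 0.87 to 0.88. With the step gradient and frailty at 1 to 2 events/year it removed more: from 1.15–1.16 to 1.05–1.06 at *r* = 2.

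**Step 6: enrolment semester added.** At 0.3 events/year the null IRR became 1.01. At about 1 event/year it was 0.98 to 1.01 across all ratios, which is 1.00 within simulation noise.

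**The case against.** **The gradient is not established.** A reader might infer from section 3.2.1 that the SAP expects early and late enrollees to have different rates. It says only that patterns are potentially different, and it concerns plots of utilisation over time. Curves by enrolment semester could differ simply because exposure starts at different dates. This objection stands: the documents give no ratio.

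**The offset is unwritten.** If each person's own rate were the response with equal weight, this bias would vanish (simulated 1.00 to 1.02). The SAP does not specify that either, and the offset is the usual way to model a rate. So the condition must be stated, but it does not remove the point.

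**The adjusted version helps.** The covariates in section 3.2.4 are those through which case mix might drift, and compound symmetry also shrinks the bias. Both reductions are real but partial for the one covariate tested; the full list was not modelled and could remove more. No listed covariate is enrolment time itself, and the 2010 counts overlap the before window from July to December 2010.

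**Precision.** It is tempting to say that the interval would falsely exclude 1. In simulation it did for ratios such as 1.5, but that depends on an assumed sample size, since the SAP gives none.

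**Reach.** A reader might think that the main result is at risk. Section 3.3.1 names the propensity-matched comparison as primary, and the time-dependent analysis in section 3.2.3 does not use these windows.

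**Conclusion.** The point holds conditionally, for a supportive analysis. The opposite-moving windows are a matter of date arithmetic and are certain. The bias needs two further conditions: weighting by person-time, and a difference in underlying rate by enrolment date.

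Under a gradual early/late ratio of 0.5 to 2.0, with uniform enrolment, no program effect and no deaths, the unadjusted null IRR lies between about 0.85 and 1.18. Its place in that range depends on event rate and frailty, and a step change would widen the range. With no gradient the bias is zero. Adjustment for 2010 use leaves part of it.

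The SAP cannot rule the gradient out in advance, and it already treats enrolment semester as worth examining. Leaving enrolment time out of the model is therefore an avoidable weakness. It is not evidence that the before-after result will be wrong.

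**What to change.** In section 3.2.2, add enrolment semester (or month) as a fixed factor in both the unadjusted and adjusted before-after models, and state log person-time as the offset. Month also removes the small remainder within semesters. The enrolment date is already defined in section 1.1, so no new data are needed.

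The cost is one extra factor. The version labelled unadjusted would then be adjusted for enrolment time and should be described so. The change does not deal with secular trend or regression to the mean.

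A conditional Poisson model with participant as stratum also gave about 1.00 to 1.02 under the null. However, deaths shorten only the after window and were not modelled, so its robustness to event-related death is not shown. It is better kept as a secondary option.

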### 3.2.3 *Time-dependent analyses*

Time-dependent analyses will be used to assess the impact of “exposure to the program” on the rate of hospitalisations. Exposure to the program will be defined for each semester as the proportion of the time a participant was exposed to the program e.g. if a patient gets enrolled into the program halfway through a semester, his/her exposure will be 50% (s/he was on the program 50% of the time during that particular semester).

The time-dependent analysis will cover a total of 6 semesters. All patients enrolled between January 2011 and December 2013 will be included and all events occurring within the same timeframe will be considered. For the purpose of this analysis every program participant will therefore contribute 6 data points; one per semester. The analysis will be a Poisson regression with the exposure proportion as a fixed effect. A sensitivity analysis will also include the semester and its interaction with exposure. Generalized estimating equations with a compound symmetry structure will be used to model the correlations between multiple measurements from each patient

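### The time-dependent analysis does not set the pre-enrolment run-up apart, so its exposure effect is biased toward benefit if admissions cluster just before enrolment

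*SAP*

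**What the plan says.** Section 3.2.3 of the SAP defines exposure as a fraction of each half-year: "Exposure to the program will be defined for each semester as the proportion of the time a participant was exposed to the program". Its illustration is that "if a patient gets enrolled into the program halfway through a semester, his/her exposure will be 50" per cent.

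On coverage, "The time-dependent analysis will cover a total of 6 semesters", and "every program participant will therefore contribute 6 data points; one per semester". The enrolment semester is therefore one record and is not divided. On the cohort: "All patients enrolled between January 2011 and December 2013 will be included and all events occurring within the same timeframe will be considered".

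On the model: "The analysis will be a Poisson regression with the exposure proportion as a fixed effect", fitted by generalized estimating equations with compound symmetry. In addition, "A sensitivity analysis will also include the semester and its interaction with exposure".

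Section 1.1 gives each participant an enrolment date by a hierarchy of three dates, starting with "If the Program consent date is available, it will be used as the enrolment date". Section 3.2.3 uses that date only to form the fraction. It defines no pre-enrolment window and states no person-time offset. Section 3.3.1 makes the propensity-matched comparison the primary analysis of program effect.

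**The concern.** A participant admitted in February and enrolled on 1 April has that admission counted at 50% exposure, exactly as if it had happened in May. If people tend to be enrolled after a spell of admissions, the rate is temporarily high before enrolment and falls back afterwards whether or not the program works. Nothing in section 3.2.3 separates that spell from ordinary unexposed time, so the fall is credited to the program.

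The other planned adjustments do not help. The prior-use covariates in section 3.2.4 are counts for 2010, which cannot capture a run-up before a 2012 or 2013 enrolment. At stake is whether this analysis can support a statement that exposure to the program reduces admissions.

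**Working it through.** **The plan's own figures.** Enrolment at month 3 of 6 gives 3/6 = 50%. January 2011 to December 2013 is 36 months, and 36/6 = 6 semesters. Both agree with the SAP.

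**Assumptions (not in the SAP).** Enrolment is uniform over 36 months, with no deaths, no calendar trend and a true rate ratio of 1.00. The run-up is a stated multiple of the baseline rate for a stated time before enrolment.

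**One semester by hand, run-up 3x for 3 months (baseline = 1).**
- Enrolled at month 5, exposure 1/6: (2×1 + 3×3 + 1×1)/6 = 2.0
- Enrolled at month 3, exposure 1/2: (3×3 + 3×1)/6 = 2.0
- Enrolled at month 1, exposure 5/6: (1×3 + 5×1)/6 = 1.33
- Any later semester, exposure 1: 1.0

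The rate falls as the fraction rises, with no program effect at all.

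**Where the run-up falls (3 months).** The mean run-up time inside the enrolment semester is (4.5 + 9)/6 = 2.25 months. The other 0.75 falls in the semester before, which is unobserved for first-semester enrollees. The share coded partly exposed is 6×2.25/(6×2.25 + 5×0.75) = 13.5/17.25 = 78%.

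**Splitting at the date without a window.** Mean unexposed time is 18 months, of which 17.25/6 = 2.875 is run-up. The unexposed rate is (15.125 + 3×2.875)/18 = 1.319, so the rate ratio is 1/1.319 = 0.758. A large-sample calculation with an independence working correlation also gives 0.758. The same calculation gives 0.886 for the planned fractional coding, so the split alone is worse.

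**Simulation of the exchangeable Poisson GEE.** This used 1 admission per year, between-person gamma variance 1 and up to 200,000 participants. Ranges are over repeat runs.

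| Run-up | Planned main model | Semester main effects added | Split at date, no window | Split, 3-month window separate |
|---|---|---|---|---|
| none | 0.99–1.00 | 0.99–1.00 | 1.00* | 1.00 |
| 3x, 1 month | 0.97–0.98 | 0.96–0.97 | 0.87–0.90 | 0.98–1.01 |
| 3x, 3 months | 0.85–0.86 | 0.74–0.76 | 0.71–0.72 | 0.98–0.99 |
| 5x, 3 months | 0.76–0.77 | 0.60–0.62 | 0.54 | 1.00 |

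*Large-sample calculation.

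With semester terms, the split without a window gives 0.82, 0.55 and 0.33 for the last three rows.

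**Dependence on heterogeneity.** For 3x over 3 months with semester added, the estimate is 0.848 with no between-person variation, 0.776 with variance 0.5 and 0.726 with variance 2.

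**The planned interaction model.** The figures with semester main effects are not outputs of this model. It was examined in the large-sample calculation with independence working correlation. For 3x over 3 months, the semester-specific rate ratios under a null effect are 1.675, 1.037, 0.919, 0.826, 0.684 and 0.399. For 3x over 1 month they run from 1.385 to 0.667. It would suggest a change of effect over time that does not exist.

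**A window shorter than the run-up.** With a 3-month window, a 6-month run-up at 3x gives 0.72 in simulation (0.56 with semester), and a 12-month run-up at 2x gives 0.65 (0.52). A hand check of the 6-month case, without between-person variation: the run-up left in the reference time is 5.5 − 2.875 = 2.625 of 15.125 months. The rate is (12.5 + 3×2.625)/15.125 = 1.347, so the rate ratio is 0.74.

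**The case against.** A reader might infer that coding exposure as a proportion is itself the error, and that restoring the enrolment date would cure it. That does not hold. With no run-up, the fractional coding returns a true 0.80 as 0.800 and a true 0.50 as 0.502. With a run-up it dilutes the bias, and the date split alone increases it. All of the gain comes from isolating the run-up.

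A reader might also infer that the SAP says admissions prompt enrolment. It does not. Section 2.2 lists source of referral and risk of hospitalisation as baseline items without linking them to enrolment. Step 2 of the matching in section 3.3.1 excludes participants with no hospitalisation in the preceding 12 months, so the plan allows for enrolments without a recent admission. The premise is plausible, but the size of the bias rests wholly on the assumed run-up.

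It can fairly be said that the analysis is supportive, that the matched outcome is counted after the matching period, and that the before-after analysis in section 3.2.2 already separates events at enrolment. The first two limit the consequence. The third gives no protection, because section 3.2.2 has no pre-enrolment window either.

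What stands is conditional: if there is a run-up, the planned model is biased toward benefit, and neither planned version of it guards against this.

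**Conclusion.** The point holds in conditional form and should be addressed, although it does not touch the primary analysis. For an assumed run-up of 3x baseline and no true effect, the planned main model would show an apparent reduction of about 2% to 3% (1 month) or 14% to 15% (3 months). With semester main effects added, this becomes 3% to 4% or 24% to 26%. With no run-up there is essentially no bias.

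These figures assume uniform enrolment, gamma variance 1 between people, no deaths and no calendar trend. The planned semester-by-exposure model is also distorted in the one calculation made, but that used a simpler working correlation, so its exact size under the planned GEE is not established.

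**What to change.** In section 3.2.3, divide each participant's person-time at the enrolment date into unexposed and exposed rows. Use days at risk as offset and 0/1 exposure. Code a prespecified pre-enrolment window as its own category, or exclude it, so that the program contrast is exposed time against earlier unexposed time. Do not adopt the split without the window.

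Name a main window length, for example 3 months, and repeat with others, for example 1, 3, 6 and 12 months. State that a window shorter than the run-up leaves bias.

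The cost is SAP wording and data-step programming; the enrolment date is already defined and admissions are dated. The statistical cost is lost reference time. Under uniform enrolment, the mean unexposed time of 18 months falls to (36 − w)²/72 for a window of w months:
- 1 month: 17.0
- 3 months: 15.1
- 6 months: 12.5
- 12 months: 8.0

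The loss falls on early enrollees. With a 12-month window, those enrolled in the first 12 of 36 months (one third) keep no reference time within the analysis period. The choice of length remains a judgement, which is why it should be fixed in advance and varied.
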